#### Cross-over study

##### Total sample

Inclusion/exclusion criteria will be, boys from 7th to 8th grades (12–13 years old) who not present any physical, psychiatric and/or psychological disability and that they have received the approval of their parents.

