##### Total sample size and power

For feasibility reasons, the school chosen for the development of exercise sessions is close to our laboratory. Sample size is estimated according to the mean difference of two independent samples from a randomized controlled trial were a working memory task (2-back) was tested [56]. Children control group achieved a positive variation (∆ = 2.05 ms; SD = 93.1) while exercise group a negative variation (∆ = − 69.45 ms; SD = 91.6) [56]. A loss rate of 20% was considered. Statistical power analysis indicated that at least 32 participants would yield adequate power (i.e., > 80%) and α (i.e., < 0.05), with a detectable variation of 71.50 ms (∆ between experimental conditions – control condition).

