#### Cross-over study

Differences among condition will be calculated using general lineal models (95% confidence) and estimating the Hedges effect size [115]. Strength of effect will be assessed according to the following interpretation: trivial (0–0.19), small (0.20–0.49), medium (0.50–0.79) and large (0.80 and greater) [116]. The significance threshold analyses will be *p* < 0.05.Regarding missing data, it is anticipated that missing data could be due to faults in the EEG and eye-tracker, and thus will be missing at random. For this reason, multiple imputation will be used to address this issue.

In addition to performance in the task of working memory and reading, several neurocognitive variables (amplitude and latency of both potentials, frequency of the alpha wave, and variation of its amplitude with the opening of the eyes) will be studied statistically using a model of mixed effects, which initially will use the factors: subject, exercise protocol and cognitive ability (high or low performer). Subsequently, it will be extended to other factors (the rest of the measures of the Cogni-Action Project, such as body composition, sexual development status, anthropometric measures, socioeconomic, brain structure, etc.), to establish which factors and interaction between them have greater statistical significance in the acute effects of PA on cognitive and academic performance.

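### The cross-over analysis sets out to establish effect modifiers by statistical significance from an open list of project measures, with no error control and little power for modification

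*Protocol article*

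**What the plan says.** The analysis is described in the protocol article under Data analysis plan, Cross-over study. A mixed-effects model is fitted first with subject, exercise protocol and cognitive ability (high or low performer). The next step reads: "Subsequently, it will be extended to other factors (the rest of the measures of the Cogni-Action Project". Five kinds of measure are named as examples (body composition, sexual development, anthropometry, socioeconomic status, brain structure), and the list ends with an et cetera. The stated aim of this step is "to establish which factors and interaction between them have greater statistical significance in the acute effects of PA on cognitive and academic performance". The only threshold in the section is p < 0.05.

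The sample size is given under Cross-over study, Total sample size and power. The basis is: "Sample size is estimated according to the mean difference of two independent samples". The conclusion is that "at least 32 participants would yield adequate power", "with a detectable variation of 71.50 ms" between experimental and control conditions, with 20% loss allowed for. No modifier or interaction enters that calculation.

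**The concern.** The sentence fixes three things together: a purpose (to establish), a candidate set (open, with interactions) and a criterion (greater statistical significance). A search over many candidates at an unadjusted 0.05 produces significant modifiers when none exist. A p-value is also a poor yardstick for the importance of a factor, because it reflects how completely a factor was measured as well as how strongly it acts. Brain MRI, for example, is planned for 76 of the 797 children, so brain structure may be available for only some of the cross-over boys.

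What is at stake is any statement about which boys respond more to exercise. The Discussion hopes that the project's results will help generate school and ministerial programmes. The main comparison between conditions is not affected.

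**Working it through.** **1. The plan's own figure.** Inputs from the sample size section: difference 2.05 + 69.45 = 71.50 ms; SDs 93.1 and 91.6, pooled √((93.1² + 91.6²)/2) = 92.35; power 80%; alpha 0.05, taken as two-sided. Then n per group = 2 × [92.35 × (1.960 + 0.842)/71.50]² = 26.19, and 26.19 × 1.2 = 31.4, so 32. The figure reproduces as the size for a single condition contrast.

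**2. How many candidates there are.** Counting only items listed in six measurement sections:

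| Section | Items |
|---|---|
| Anthropometry | 11 |
| NeuroCognitive Performance Test tasks | 8 |
| School subjects graded | 9 |
| Sleep self-report subscales | 4 |
| Quality-of-life dimensions | 5 |
| School stress dimensions | 3 |
| **Total** | **40** |

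This leaves out body composition, maturity, socioeconomic status and brain structure. The number that would enter the model is not stated, so 5, 10 and 20 are used below as assumptions.

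**3. Chance of at least one false modifier, one outcome, no true modifier.** With k independent tests at 0.05 it is 1 − 0.95^k:

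- k = 5: 0.23
- k = 10: 0.40
- k = 14: 0.51
- k = 20: 0.64

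Measures taken on the same boy are correlated, which lowers these values. A simulation used three conditions per boy, 26 or 32 boys, continuous factors with pairwise correlation 0 to 0.5, and each factor tested separately by a 2-df protocol-by-factor F test (3,000 runs per cell):

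| Factors | Chance of at least one false modifier |
|---|---|
| 5 | 0.19–0.23 |
| 10 | 0.31–0.40 |
| 20 | 0.44–0.65 |

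A repeat with a different random seed agreed within about 0.02. Results for 26 and 32 boys were similar.

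Adding interactions between factors raises the count quickly. Ten factors have 10 × 9/2 = 45 pairs, so 55 tests, and 1 − 0.95^55 = 0.94 under independence.

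**4. Power for a modifier.** Take the correlation ρ between a factor and a boy's exercise effect. By Fisher's z, 80% power needs atanh(ρ) = (1.960 + 0.842)/√(n − 3):

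- n = 32: 2.802/√29 = 0.520, so ρ = 0.48
- n = 26 (after 20% loss): 2.802/√23 = 0.584, so ρ = 0.53

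For a true ρ of 0.2 and n = 32: atanh(0.2) × √29 = 0.203 × 5.385 = 1.09, and power = Φ(1.09 − 1.96) = 0.19.

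**5. Overstatement.** With 32 boys an observed correlation must exceed about 0.35 in size to reach p < 0.05. A true 0.2 can therefore be significant only if it is overestimated or has the wrong sign. By simulation its average size among significant results is about 0.43, roughly double the truth.

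**6. The same on the millisecond scale.** Suppose a modifier splits the boys 16 v 16, and let r be the assumed within-boy correlation between conditions. The SD of a boy's condition difference is 92.35 × √(2(1 − r)), which is 130.6, 92.35 and 71.5 ms for r = 0, 0.5 and 0.7. Power is 32%, 56% and 78% if the modification is as large as the whole 71.50 ms effect, and 12%, 19% and 28% if it is half that.

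**The case against.** The best defence is that this is a condensed article with loosely worded English. The plan is staged, with a three-factor model first and the extension second. The Background says that the project will explore the acute effects. No modifier is listed among the cross-over primary outcomes. A list of modifiers and a multiplicity method are details that a fuller protocol or analysis plan may carry, and sizing a trial on the main contrast alone is normal when modifier analyses are secondary.

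Much of this stands. The absence of a list or an adjustment method would not by itself be a finding. What remains is the criterion that the article does state: to establish factors by greater statistical significance. A general remark that the project explores acute effects does not label this step exploratory, and a later document would have to depart from the stated aim to repair it.

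The objection also rules out several stronger readings that a reader might infer:

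- *That the small sample causes the false positives.* With valid tests, the number of tests drives them. The 32 boys limit power and inflate the estimates that pass the threshold.
- *That most reported modifiers would be chance findings.* This needs an assumed share of true modifiers, which the documents do not give.
- *That a false modifier is more likely than not in every case.* Five factors on one outcome give only about 0.2. One half is passed at about 14 independent tests.
- *That a list of boys who benefit more will be used for policy.* The Discussion voices only a general hope about the whole project.

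The calculations use separate tests, whereas the article extends one model, so they indicate size and do not replicate the planned analysis. Forbidding interactions between factors, or requiring a ranking by standardised estimate, would be a preference and is not asked for.

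**Conclusion.** The point holds in a limited form. The stated rule is an unadjusted search for effect modifiers over an open list, with the aim of establishing them. Every probability depends on how many factors are tested, which the article leaves open: about 0.19–0.23, 0.31–0.40 and 0.44–0.65 per outcome for 5, 10 and 20 factors. These values assume separate tests, no true modifier, and correlations of 0 to 0.5 between factors. With at least 40 measures listed, a false modifier is likely if the search is run as broadly as it is written. It need not be likely if only a handful of factors are used.

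Low power is a second and distinct weakness. At 32 boys only a correlation of about 0.48 or more is detected with 80% power, so weaker modifiers will mostly be missed, and those declared significant will look too large. The change should be made.

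**What to change.** In Data analysis plan, Cross-over study, replace the clause about establishing factors and interactions by statistical significance with wording such as: *Effect modification by other project measures is exploratory. A short list of modifiers is fixed before analysis. Each is tested as a protocol-by-factor interaction and reported as an interaction estimate with its 95% confidence interval and a false-discovery-rate adjusted p-value. Any factor-by-factor interactions are also exploratory. No modifier will be claimed as established.*

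The cost is that modifier results can no longer be presented as established. The team must also agree the short list in advance and do a little more analysis work. No extra participants or measurements are needed.

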##### Data management

Data for all participants will be stored in coded form. The codification will be perform by a researcher of team and will be stored online to avoid any issue. The senior researcher will be control the shared of data with another researchers. As the intervention have only acute characteristics, any adverse event will be controlled immediately by researcher team in the place of is carry out the intervention.

##### Dissemination of results

The research team will be access to both cross-sectional and RCT dataset. Additionally, the senior researcher ([name]) could share the database previous request. Each participant will know your general results if parents ask it and any medical findings are timely informed. Outcomes from the study will be published in peer-reviewed academic journals as well on scientific meetings and social media.

## Discussion

### Expected results and transfer to the school context

Nowadays, both education and health are two of the most relevant concerns worldwide [117]. Thus, during the last years, a great interest has generated to establish the association among PA, sedentarism, and physical fitness on brain structure and function [4, 53], assuming that to some extent; it could be transferred to the scholar success. However, there is a lack of scientific evidence based on advanced neuroimaging and neuroelectric techniques (e.g., MRI, EEG), and objective methods to measure PA (e.g., ACC) in developing countries.

Regarding the educational context, the contributions of this project will cover two important aspects in order to improve both academic achievement and cognitive performance. The first aspect is related to establish general recommendations due to the poorly understanding about PA dosage linked to brain health [118]. For this, a complete analysis will be performed with the intention to understand which factors, such as time and type of PE lessons and recesses, intensity of PA, effectiveness of PE, time on sedentary behaviours, physical fitness components (e.g., strength, cardiorespiratory fitness or speed-agility fitness), time of day to perform PE (e.g., morning or afternoon) are more related to a better academic achievement and cognitive performance. Furthermore, we will test the mediation influence of vulnerability index, type of schools (financing system), perception of school stress, among others. This is an important topic to study due to the great social inequalities in Chile.

The second aspect, it about the negative acute physiological effect of sedentary behaviours (typical class of school), in contraposition with the hypothesised positive influences of different models of PE lessons on working memory and reading [48]. Thus, PE could be used as a learning enhancer for important subject such as mathematics, languages, and others [27]. Hence, this project will also allow advancing in the understanding about the underlying bases of acute effects of a single bout of PA on spontaneous brain activity and cognitive performance during different cognitive task. Likewise, whereas our proposed intervention is not in a real school environment, the design of this experimental study has based its methodology emulating the times and activities that are usually carried out in schools.

Finally, we hope that the results of this project will help to generate future programs and interventions both at the ministerial and at the local level (schools) in order to improve the physical health and cognitive and academic performance of schoolchildren.

The “Cogni-Action Project” will try to identify efficient ways to improve academic achievement and cognitive performance in youth trough PA during the school day as well as during the rest of the day. To our knowledge, this project will be the first cross-sectional study using neuroimaging and objective PA measures in Latin-America, which also incorporates another study about the acute effects of PA and sedentarism on cognition and brain activity. We hope this work will be considered a step forward in searching ways to improve children and adolescents’ health and to reduce educational and overall inequalities in developing countries.

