Regarding the last point, the Chilean’s education system is harshly criticized due to the privatization of schools, the voucher system based on average attendance, the creation of incentives and penalties for schools and teachers [37]. These characteristics increase the inequality among students, which initially is originated by a well-known socioeconomic status gap. Indeed, the Chilean educational system estimates the school vulnerability index (SVI), which is an indicator of the degree of educational establishment vulnerability (ranging from 0 to 100, indicating what percentage of students presents in an unfavourable socioeconomic status and therefore, they become priority for the government policies) [38]. Despite the above the Chilean education system is one of the highest-performing in Latin-America but it also presents one of the highest within-country variability in outcomes [39]. In this line, there is a strong relationship between student achievement, socioeconomic status, and financing system of schools [40].

In other context, most of evidence trying to explain the underling mechanisms by which PA improves cognitive and brain functioning have been performed in developed countries [17, 41, 42] and in a well-controlled laboratory settings [43–45]. But, it is also important to develop cross-sectional studies in a more unfavourable sociocultural context as well as experimental studies in a more realistic environment to ensure the integration into the education field.

Experimental trials recently published show that cognitive-related brain activity (e.g., EEG [electroencephalography] oscillations and event-related potentials) is acutely modified after a single bout of PA, boosting cognitive performance in adults [43–46] and children [45]. Whereas there are several mechanisms by which an acute bout of PA can improve brain functioning or cognitive performance, various issues remain unclear [47]. In fact, to date there is not consensus about dose, intensity, duration and type of the PA that better improves brain and cognitive performance, or how long does this effect persists after a single bout of PA [48].

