**Fig. 1 Fig1:**
[figure not shown]
Cross-sectional and cross-over RCT study design

During the first part (i.e., cross-sectional study), measurements will take place in public and private schools, with two visits of 4 h each separated by 8 days. At the first visit, questionnaires, cognitive performance and anthropometric measurements will be assessed, followed by accelerometers placement. During the second visit, physical fitness and other questionnaires will be evaluated, plus accelerometer removal. A detailed description of all evaluations can be found in the measurements section.

Regarding the second part (i.e., crossover-randomized trial), children will be randomized to each protocol session, participating in all of them with two-weeks apart. Thus, they will assist to our gym to perform one of the three protocol and subsequently they will be move to a laboratory where they will undergo EEG and eye-tracking measurements during resting state condition and during two different cognitive tasks. More details can be found in following sections.

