#### School characteristics

Several characteristics of school will be registered such as SVI, scholar schedule, public or private administration, location, and educative project.

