### Data analysis plan

#### Cross-sectional study

Descriptive data from participants will be summarized separately for boys and girls, and presented as means and standard deviations for continuous variables and as percentages for categorical variables. T-test or chi-square analysis will be used to establish sex differences where appropriate. Also, interaction analysis by sex will be performed previous to the main analysis.

Given that the first aim of the project is to associate PA, sedentarism, and physical fitness with brain structure and function, cognitive performance and academic achievement; general linear models will be employed. Additionally, multilevel random-effects models will be used. Furthermore, as knowledge about this relationship in Chilean population is scarce, mediation analyses will be performed with other relevant variables related to school context. The significance threshold for all analyses will be *p* < 0.05.

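### The school vulnerability index and school financing type are listed as mediators, although a child's activity or fitness cannot change either; they are potential confounders or effect modifiers

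*Protocol article*

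**What the plan says.** The data analysis plan for the cross-sectional study states that "the first aim of the project is to associate PA, sedentarism, and physical fitness with brain structure and function, cognitive performance and academic achievement". It names general linear models and, in addition, multilevel random-effects models, and then says that "mediation analyses will be performed with other relevant variables related to school context". The Discussion, under Expected results and transfer to the school context, names some of those variables: "we will test the mediation influence of vulnerability index, type of schools (financing system), perception of school stress, among others".

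The Background describes the vulnerability index as a 0 to 100 measure of the school, "indicating what percentage of students presents in an unfavourable socioeconomic status". Under School characteristics, the article records the index and the type of administration as properties of the school: "Several characteristics of school will be registered such as SVI, scholar schedule, public or private administration, location, and educative project". On the link with the outcome, the Background says that "there is a strong relationship between student achievement, socioeconomic status, and financing system of schools". The article gives neither the index nor school type a role as covariate, confounder or moderator in these models.

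**The concern.** A mediator has to be affected by the exposure. A pupil who becomes more active or fitter does not change the share of disadvantaged pupils in the school or the way the school is financed. The article's own account places these features upstream. After describing the school system, it says: "These characteristics increase the inequality among students, which initially is originated by a well-known socioeconomic status gap".

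The data cannot correct a wrongly assigned role. The study is cross-sectional, "with two visits of 4 h each separated by 8 days". In a linear model, a mediator and a common cause give the same product of coefficients, so only the role chosen in advance decides whether that product is read as a pathway or as confounding. The article hopes to inform school programmes at ministerial and local level. A statement that activity acts on achievement through school vulnerability would be a misleading basis for that.

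**Working it through.** The point concerns causal order, and the article gives no figure to reproduce. The check has two parts: the ordering, and the consequence of getting it wrong.

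**Ordering, from the article**

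| Variable named for mediation | How the article defines it | Can one child's activity change it? |
|---|---|---|
| Vulnerability index | Percentage of the school's pupils who are disadvantaged | No |
| School type | Financing system of the school | No |
| Perceived school stress | The child's own questionnaire response | Plausibly yes |

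The index takes one value per school, so within a school it cannot vary with a child's activity. Any index-activity association lies between schools.

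**Algebra.** Let S be the index, PA activity and Y achievement, all standardised. Suppose S causes both and PA has no effect on Y:
- PA = a·S + error and Y = b·S + error.
- Regressing S on PA gives slope a. Regressing Y on PA and S gives 0 for PA and b for S.
- Indirect effect = a × b. Unadjusted total effect of PA on Y = a × b. The indirect effect is therefore exactly the confounding, and the apparent proportion mediated is 100%.
- Example: a = -0.2, b = -0.4 gives 0.08 for both.

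**Simulation inputs.** n = 664, which with the article's 20% dropout addition gives its 797 (664 × 1.2 = 796.8). Two-sided 0.05 (the article states p < 0.05 without sidedness). There were 1,000 replicates with a single-level Sobel test, z = ab / √(a²·SE_b² + b²·SE_a²). S was drawn either per child or shared within 20 schools. The correlations and the number of schools are assumptions, because the article gives none.

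| Assumed index-activity / index-achievement correlation | False indirect effect, index per child | False indirect effect, index shared in 20 schools |
|---|---|---|
| 0 / 0.4 | 4.0% | 3.8% |
| -0.1 / -0.3 | 71.6% | 64.2% |
| -0.1 / -0.4 | 76.1% | 70.4% |
| -0.2 / -0.4 | 100% | 99.3% |
| -0.3 / -0.5 | 100% | 100% |

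**Hand check of the -0.1 / -0.3 row, index per child**
- SE_a = √(0.99/662) = 0.0387, so a/SE_a = -2.59.
- SE_b = √(0.91/(661 × 0.99)) = 0.0373, so b/SE_b = -8.04.
- z = 1/√(1/2.59² + 1/8.04²) = 2.46.
- Probability of exceeding 1.96 is about Φ(0.50) = 69%, close to the simulated 71.6%.

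**After the change.** With S entered as a covariate in the same data, the mean PA coefficient is about 0.00, and it is significant in 4.6% to 5.9% of replicates in the rows where S is related to PA.

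**Total effect.** In a single-level unadjusted model with n = 797, a true correlation of 0.08 gives z = 0.08 × √795 = 2.26 and significance in about 62% of samples. A separate simulation used about 800 children, with the index shared within 10, 20 or 40 schools (assumed), a = -0.2 and b = -0.4. It gave 52% to 59% by simple regression but 5% to 9% with a random intercept for school. That run had only 200 replicates per cell, and some fits gave convergence warnings, so its figures are rough.

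**The case against.** Four points can be made for the plan.

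- **The analysis plan itself does not name the index or school type.** They are tied to mediation in one Discussion sentence, which also names perceived stress, a reasonable mediator. That is so. But the sentence is a commitment to test, and the analysis plan contains the same kind of analysis in general terms, so it is more than a passing remark.
- **Mediation may be a loose word for moderation.** The sentence is followed by a reference to social inequality in Chile, which would fit asking whether the association differs between schools. If so, the text still specifies the wrong analysis and needs correcting.
- **The index-activity link is not in the article.** It links socioeconomic status and financing to achievement only. This stands: without that link, false mediation occurs at about 4%, and the harm does not arise.
- **The covariate set may be in an analysis plan that is not shown.** School characteristics and family socioeconomic status are collected, so nothing rules out adjustment. This also stands. The point is the role that the article does assign, not the missing covariate list.

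A reader might go further and infer that the project will report a confounded total effect as the effect of activity. The article does not support this. It also plans multilevel models, and if school is the random effect (the level is not named), much of the between-school confounding of the total effect may be removed. The 62% above belongs to a single-level unadjusted model only.

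**Conclusion.** The point holds. The vulnerability index and financing type are given a role that they cannot have on the article's own definitions, whatever the data show. The size of the consequence depends on an association that the article does not report: a false indirect effect in about 64% to 76% of samples at an assumed index-activity correlation of -0.1, close to 100% at -0.2, and about 4% at zero. These figures assume linear relations, no true activity effect and a single-level mediation test.

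A reader might also infer that confounding is certain to be published as a mechanism. The article does not say so. It describes its first aim as association, and how the result would be worded is unknown. This should be fixed but does not undermine the project. It concerns the cross-sectional part only; the randomised crossover is unaffected.

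**What to change.** - Remove the vulnerability index and school type from the variables to be tested as mediators.
- Enter both as school-level covariates, together with family socioeconomic status, in the association models and the mediation models. State that school is the random-effect level if that is intended.
- If the question is whether the association differs between kinds of school, test it with an exposure-by-index or exposure-by-school-type interaction, and call it effect modification.
- Keep mediation for variables that activity could plausibly change, such as perceived school stress or sleep, and describe the results as cross-sectional associations.

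The cost is a revision of the analysis text. The index, the type of administration and family socioeconomic status are already to be collected, and neither sample size nor visits change.
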